### Participant Timeline

The FRAILMar participant timeline is summarized in Figure 2. Enrolment started in September 2020 and will continue until December 2022. The baseline assessment will be carried out on three different days (A-1, A-2, and A-3). A-1 and A-2 will take place in the Rehabilitation Department and A-3 in the Nephrology, Endocrinology, and Internal Medicine Departments, as shown in Table 2. The study tests and questionnaires will be administered as detailed in Figure 1.

**Figure 2 F2:**
[figure not shown]
The FRAILMar Study Flow-diagram.

**Table 2 T2:** Baseline assessment: sequence of examinations and delivery of questionnaires.

A-1 Day 1	Clinical visit	• Anamnesis • Charlson Comorbidity Index • Frailty stratification (Fried phenotype) • SARC-F screening tool • Barthel Index • Lawton Instrumental Activities of Daily Living Scale
	Examinations carried out in the Rehabilitation Department	• Bioelectrical impedance analysis (InBody S10) • Muscle ultrasound (forearm, quadriceps, and intercostal muscles) (Esaote MyLabSeven^®^) • Dominant handgrip isometric contraction (Jamar^®^ Plus) • Dominant quadriceps isometric contraction (Mecmesin^®^) • Four-meter gait speed • 6-min walking test • Respiratory muscle pressures (MicroRPM) • Cardiopulmonary effort test
	Delivery of self-administered questionnaires	• Minnesota Leisure-Time Physical Activity Questionnaire (short form) • Malnutrition Universal Screening Tool • Hospital Anxiety and Depression Scale • Generalized Anxiety Disorder seven-item questionnaire • Center of Epidemiological Studies Depression • Five Facets Mindfulness Questionnaire • Temperament and Character Inventory 140 • Short Form 36-item health questionnaire
	Delivery of activity monitors	• Actigraph GT3-x
A-2 Day 7	Frailty measures other than Fried phenotype	• Frail Scale • Clinical Frailty Scale • Edmonton Frail Scale • Frail-VIG Index
	Return of activity monitors	• Actigraph GT3-x
A-3 Day 7–14	Other assessments	• Laboratory blood tests • Dual-energy X-ray absorptiometry (Hologic Horizon Wii) • Nutritional assessment: anamnesis, anthropometry

The first baseline assessment (A-1) will last nearly 3 h and will be divided in three parts:

Clinic visit: Frailty assessment, anamnesis and physical examination with clinical history will be carried out by a physiotherapist who will explain the multimodal prehabilitation details and answer patient questions about the trial. The Fried Phenotype will be used to stratify participants as non-frail (0–1 items) or frail (2–5 items) prior to randomization.Battery of tests carried out in the Rehabilitation Department, in sequence: BIA, ultrasound of the intercostal, forearm and quadriceps muscles, isometric dynamometry, four-meter gait speed test, 6MWT, maximal respiratory muscle pressures, and CPET.Delivery of self-administered scales and activity monitors: Immediately after completing the test battery, a set of self-administered questionnaires (malnutrition screening, anxiety and depression symptoms, mindfulness dispositional traits, personality traits, and health-related quality of life) will be delivered to patients to be completed during the following week. Activity monitors to record daily physical activity for the next 7 days also will be delivered.

The second baseline assessment (A-2) will be carried out 1 week later, when patients return the self-administered questionnaires and activity monitors. During this second visit, frailty will be assessed with the use of frailty measurement tools other than the Fried phenotype.

The third baseline assessment (A-3) will consist of laboratory blood tests, DXA, and a visit with a nutritionist. Based on anthropometry, diet history, alimentary habits, nutritional requirements, BIA reports conducted in A-1, and scores from the malnutrition screening tools, patients will be classified as having severe malnutrition, moderate malnutrition, overweight/obesity, and good nutrition status. Further nutritional controls will be scheduled for week 12 and every 6 months until KT.

### Sample Size

Sample size is calculated to identify significant differences in overall bad-outcome in KT recipients. Accepting an α risk of 0.05 and a β of 0.2 in two-sided testing, 38 frail participants (19 in each group, intervention and control) will be necessary to recognize as statistically significant a decrease of 25% in bad outcomes. The sample size has been overestimated to allow potential losses of 20%, requiring a final sample of 46 patients (23 in each group). Similarly, 76 non-frail patients (38 in each group, intervention and control) will be necessary to recognize as statistically significant a decrease of 12.5% in bad outcomes. Given the patient mortality after listing, the potential for exclusion from the kidney transplant waiting list due to medical issues, and the possibility of voluntary drop-out, 20% of potential losses has been considered to estimate a final sample of 92 (46 in each group). Therefore, sample size in the FRAILMar study will be of 138 participants.

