## Abstract

**Introduction:** Frailty is very frequent among patients with chronic kidney disease (CKD) who are awaiting deceased donor kidney transplantation (KT), and transplant outcomes are worsened in those frail recipients. Frailty and poor fitness powerfully predict mortality, kidney graft survival, and healthcare utilization after KT. Intervention is essential to improve survival and quality of life for frail CKD patients, regardless of their age. Studies of post-transplant physical therapy intervention have been met with limited success, in large part due to high dropout rates. A pre-transplant clinical framework for multimodal prehabilitation interventions including physical therapy, nutritional measures, and psychological support scheduled during the KT waiting list period may improve patient retention and compliance, better mitigate the effects of frailty and poor fitness after KT, and improve main outcomes in frail CKD patients.

**Main Objective:** To study the effectiveness, feasibility, and safety of multimodal prehabilitation (exercise, nutritional plans, psychological advice) in KT candidates.

**Methods:** Randomized controlled clinical trial in 38 frail and 76 non-frail KT candidates. The prehabilitation program will consist of physical exercise (24 sessions, 8 weeks), nutritional supplementation, and psychological advice. The primary endpoint will be a composite achievement of clinical and functional main outcomes in frail and non-frail KT candidates at 90 days post-transplantation. Secondary outcomes include changes in exercise capacity, physical activity, gait speed, respiratory and peripheral muscle strength, muscle size, body composition, performance in activities of daily living (basic and instrumental), anxiety and depression symptoms, and health-related quality of life. Feasibility of the intervention will be also analyzed.

**Expected Results:** Multimodal prehabilitation is a feasible and effective intervention to decrease bad outcomes at 90 days post-KT by 25 and 12.5% in frail and non-frail patients, respectively.

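### The 20% loss allowance is added as a multiplier of 1.2 instead of a division by 0.8, so the planned 138 covers about 17% losses (minor but definite arithmetic error)

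*Protocol article*

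**What the plan says.** In the protocol article, the Sample Size section sets the error rates ("Accepting an α risk of 0.05 and a β of 0.2 in two-sided testing") and states a separate requirement for each stratum. For the frail, "38 frail participants (19 in each group, intervention and control) will be necessary"; for the non-frail, "76 non-frail patients (38 in each group, intervention and control) will be necessary".

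It then adds an allowance for losses. For the frail: "The sample size has been overestimated to allow potential losses of 20%, requiring a final sample of 46 patients (23 in each group". For the non-frail, after naming death on the list, removal from the list and voluntary withdrawal as the sources of loss: "20% of potential losses has been considered to estimate a final sample of 92 (46 in each group". The section concludes that the "sample size in the FRAILMar study will be of 138 participants".

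The Methods part of the abstract describes the trial differently: "Randomized controlled clinical trial in 38 frail and 76 non-frail KT candidates".

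**The concern.** An allowance for losses exists so that, after the assumed share of enrolled patients has dropped out, the number the calculation requires is still there. That calls for dividing the required number by one minus the loss rate. Multiplying by one plus the loss rate always gives a smaller figure, and the enrolled sample then misses its target at the very loss rate it was meant to absorb.

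Both strata are affected. Each has its own target effect and its own required number, so neither can lend patients to the other. The Discussion itself expects that adherence could be low and dropout high, so the allowance may well be tested.

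A second, related matter is that the abstract attaches the required numbers to the randomised candidates and does not mention the allowance. The abstract and the Sample Size section therefore give different trial sizes.

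**Working it through.** **Inputs, all from the Sample Size section:** required per group 19 (frail) and 38 (non-frail); required per stratum 38 and 76; loss rate d = 0.20; enrolled 46 and 92, total 138.

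**Step 1: reproduce the plan's figures.** Multiply by (1 + d) per group and round up:
- Frail: 19 × 1.2 = 22.8 → 23 per group, 46 in the stratum.
- Non-frail: 38 × 1.2 = 45.6 → 46 per group, 92 in the stratum.
- Total: 46 + 92 = 138.

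This matches exactly. Division by 0.8 does not give the stated figures (step 4).

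**Step 2: who remains after a 20% loss.** Enrolled × (1 − d):
- Frail: 46 × 0.8 = 36.8, against 38 (short by 1.2).
- Non-frail: 92 × 0.8 = 73.6, against 76 (short by 2.4).
- Overall: 138 × 0.8 = 110.4, against 38 + 76 = 114 (short by 3.6).

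**Step 3: the loss rate the plan does cover.** 1 − 38/46 = 1 − 76/92 = 0.174, or 17.4% in each stratum.

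**Step 4: what a 20% loss would need, taking 38 and 76 as given.** Divide by (1 − d) per group and round up:
- Frail: 19/0.8 = 23.75 → 24 per group, 48 in the stratum.
- Non-frail: 38/0.8 = 47.5 → 48 per group, 96 in the stratum (76/0.8 = 95 on the stratum total; 96 keeps the arms equal).
- Total: 48 + 96 = 144, six more than 138.

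**Step 5: effect on power.** Assume that 19 and 38 per group give exactly 80% power at two-sided α = 0.05. With the same effect and a fraction f of the required patients, power ≈ Φ[(1.960 + 0.842) × √f − 1.960]. Here f = 18.4/19 = 36.8/38 = 0.968, so power ≈ Φ(0.797) = 0.787 in each stratum, a loss of about 1.3 percentage points.

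**Step 6: the abstract.** Its two strata sum to 38 + 76 = 114, against 138 in the Sample Size section, a difference of 24.

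**The case against.** The strongest reply concerns the denominator. The section does not say what the 20% is a percentage of. Read as a margin on the required number, it works: 20% of 38 is 7.6, and 46 − 7.6 = 38.4; 20% of 76 is 15.2, and 92 − 15.2 = 76.8. But the losses the section names (death after listing, delisting, withdrawal) happen to enrolled patients. The calculation is for transplant recipients with an endpoint at day 90 after transplantation, so a patient lost before transplantation cannot supply it. The natural denominator is those enrolled.

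The second reply is about size, and it stands. The 20% is a round planning figure with no data behind it in the article, and actual losses could differ from it by more than the 2.6-point gap between 20% and 17.4%. The frail figure alone is only two patients away from 48. No estimate, test or conclusion changes. A reader might infer that the trial is materially underpowered because of this slip; the arithmetic does not support that.

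Third, a reader might take 144 as the right size for this trial. It is right only if 38 and 76 are. The section gives no control-group rate and does not say whether "a decrease of 25% in bad outcomes" is absolute or relative, so the base numbers cannot be reproduced from it. For the same reason, exact power at 37 and 74 cannot be computed from the article. The present point takes the base numbers as the plan states them and does not vouch for them.

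Finally, the abstract's figures are the same ones the Sample Size section calls necessary, so a reader of the whole article can reconcile the two. A reader might infer that two different trials are planned, or that only 114 will be randomised; the Sample Size section rules that out. For someone who reads only the abstract, the inconsistency is real.

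**Conclusion.** The point holds as a minor but definite arithmetic error. At the stated 20% loss, the 46 frail and 92 non-frail enrolled leave about 37 and 74 evaluable patients, not the 38 and 76 declared necessary; 138 covers about 17% losses. The shortfall is 3.6 patients overall, and power would be about 79% in place of 80%.

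This rests on two assumptions: that 20% refers to enrolled patients, which the listed causes of loss support, and, for the power figure and the total of 144, that 38 and 76 are themselves sound. The finding that 46 and 92 fall short of the plan's own targets at 20% loss needs only the first. The mismatch between abstract and text is a reporting inconsistency in current wording and should be cleared up at the same time.

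**What to change.** In the Sample Size section, restate the allowance in one of two ways:

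- 46 + 92 = 138 enrolled allows for about 17% losses; or
- at 20% losses about 37 frail and 74 non-frail patients are expected to be evaluable, and power falls slightly below the stated 80% (about 79% if 38 and 76 do give 80%). An exact figure needs the assumed control-group rate, which should then be given.

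In the abstract, give 138 randomised (46 frail, 92 non-frail), with 38 and 76 as the evaluable targets.

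The cost is one sentence in each place and a slightly less favourable loss allowance or power figure. No extra enrolment is required. If the sponsor prefers to keep both the 20% allowance and the full 38 and 76, the price is six more patients, conditional on those base numbers.

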### Recruitment

Every year, around 100–120 patients receive a KT from deceased donor in the study setting; thus it is realistic to reach the target sample size during the study period. Strategies for recruiting will be similar to those described to improve adherence to interventions. Efforts will be focused on offering schedule flexibility and involving professionals able to motivate patients and clearly explain anticipated benefits of the multimodal intervention.

### Allocation

**Sequence generation:** A random number generator program will be used to allocate patients to the intervention and control groups for each stratum: non-frail or robust (Fried scores 0–1) and frail (Fried scores 2–5).

**Allocation concealment mechanisms:** Allocation concealment will be ensured as the person in charge of randomization will not release the randomization codes until participants have completed all baseline measurements.

**Implementation:** A clinician blinded to patient identification will generate the allocation sequence, doctors and nurses from the Nephrology department will enroll potential participants, and the physical therapists in charge of assessments A-1 and A-2 will assign participants to the interventions.

### Blinding

As usually happens in exercise-based interventions, participants and therapists cannot be blinded after assignments. Moreover, researchers in charge of interventions will be involved in most assessments; therefore, the FRAILMar study is an open trial except for researchers in charge of data analysis.

### Data Collection, Management and Analysis

#### Data Collection Methods

Data collection sheets will be used by the researchers in charge of collecting the study variables. These researchers will periodically update the database created by one of the principal investigators, and data collection sheets will then be stored according to current regulations. Processes to promote data quality include administration of questionnaires and tests following the same sequence, to minimize intra-rater reliability by using the mean value of three reproducible measures (e.g., muscle ultrasound parameters), and use of the highest value of three reproducible measures for outcomes requiring volitional maneuvers. Moreover, the researchers in charge of assessments will carry out a 3-day training on standardized protocols. To promote retention of participants, the physical therapists will coach participants through the follow-up period and will make telephone contact in the days before each assessment.

#### Study Instruments

**Frailty measures:** (a) Fried Phenotype: The five frailty criteria described by Fried are weight loss, exhaustion, low physical activity, slowness, and weakness; their sum score classifies individuals as not frail (score 0), pre-frail (score 1–2) and frail (score 3–5) (32); however, in renal populations patients have been categorized as follows: 0–1 as robust, two pre-frail and ≥3 frail. In addition, pre-frail and frail categories are usually joined and those patients are considered as frail; (b) FRAIL Scale: Five yes-no items addressing fatigue, resistance (cannot climb one flight of stairs), aerobic (cannot walk one block), illnesses (more than 5), and loss of weight (more than 5% in the last 6 months); patients are classified in robust (score 0), pre-frail (score 1–2), and frail (score 3–5) (34); (c) Clinical Frailty Scale: This is a nine-point scale that classifies individuals from very fit (score 1) to terminally ill (score 9) (35, 36); (d) Edmonton Frail Scale: This 12-item scale covers nine frailty domains (cognition, general health status, functional independence, social support, medication use, nutrition, mood, continence, and functional performance); the total score ranges from 0 to 17 and classifies patients as non-frail (score 0–5), vulnerable (score 6–7), mild frailty (score 8–9), moderate frailty (score 10–11), and severe frailty (score 12–17) (37); and (e) Frail-VIG index: This is a scale ranging from 0 to 1, where scores from 0.2 to 0.25 indicate frailty (38).

**Cardiopulmonary effort test:** The incremental CPET will be conducted on a cycle ergometer connected to a gas analyser and a 12-lead electrocardiogram, using blood pressure and pulse oximeter monitoring. Measurements will be taken at rest, pedaling without any resistance for 2 min, pedaling against a continuously increasing resistance, and in the recovery phase 2 min after exercise according to recommendations by the American Thoracic Society (ATS) (39). A CPET computer software package will be used; predicted normal values will be calculated.

**Six-min walking test:** The test will be performed along a 30-m flat straight corridor for 6 min according to ATS testing standards (40), using the VyntusTM Walk (Vyaire Medical, California, US) system.

**Accelerometry:** Participants will be requested to wear an adjustable cotton fabric wristband containing the Actigraph GT3-x monitors for 7 consecutive days (31, 41).

**Minnesota Leisure-Time Physical Activity Questionnaire (MLTPAQ):** This is a valid and reliable questionnaire to quantify energy expenditure during leisure time in persons older than 50 years. The MLTPAQ consists of six questions administered in an interview of around 5 min and has been validated for the Spanish population (42).

**Four-meter gait speed test:** Gait speed will be tested according to standardized methods at usual pace in a four-meter corridor; gait speed <0.8 m/s is considered reduced (43).

**Isometric dynamometers:** The Jamar^®^ plus hand dynamometer (Performance Health Supply, Cedarburg, USA) and the digital dynamometer Mecmesin AFG 500N (Mecmesin, West Sussex, United Kingdom) will be used to determine maximal isometric contraction of finger flexor and quadriceps muscles, respectively. The highest value of three reproducible maneuvers (<10% variability between values) will be used for analysis following standardized methods (44, 45).

**Respiratory muscle pressure meters**: PImax will be measured at mouth during a maximum effort from residual volume to an occluded airway; PEmax will be determined from total lung capacity in the face of the occluded airway by using the MicroRPM pressure transducer (MicroMedical/Carefusion, Kent, United Kingdom) and expressed as a percentage of the reference values determined for a Mediterranean population (46).

**Bioelectrical impedance:** BIA parameters will be assessed with the InBody S10 device (InBody Co. Ltd, Seoul, Korea).

**Dual X-ray Absorptiometry:** Total body DXA will be determined using the Hologic Horizon Wi, (Hologic^®^, Marlborough, USA) device for the measurement of body composition (fat mass and muscle mass).

**Muscle ultrasound (dominant forearm, quadriceps, and intercostal muscles): Muscle** quantity and quality according to the SARCUS recommendations (47) will be assessed using B-mode on the Esaote MyLabSeven imaging system (Esaote, Genoa, Italy) with a 5-cm wide 7.5-MHz linear probe.

**Barthel Index:** Ordinal scale that measures function independence in feeding, moving from chair to bed, grooming, transferring to and from a toilet, bathing, walking on a level surface, going up and down stairs, dressing, and continence. The score of each of the items are summed to create a total score ranging from 0 to 100, with lower scores indicating more dependence (48).

**Lawton Instrumental Activities of Daily Living Scale:** Instrument developed to assess independent living skills; there are eight domains of function and scale range goes from 0 (low function, dependent) to 8 (high function, independent) (49).

**Satisfaction scale:** A five-level Likert scale created by researchers for this study. Patients shall indicate a response to three statements on the basis of a 5-level Likert scale: (1) I am very satisfied with the overall prehabilitation program; (2) I think this program has helped me to improve my physical status; and (3) It has been easy to combine the prehabilitation program with my daily life.

**Malnutrition Universal Screening Tool (MUST):** This is a five-step screening tool to identify malnutrition, risk of malnutrition, and obesity based on body mass index, weight loss, and harmful effect of acute disease on meeting oral nutrition requirements for more than 5 days (50).

**Hospital Anxiety Depression Scale:** The HADS consists of two seven-item subscales assessing two domains (anxiety and depression, respectively). The Spanish version of the HADS has demonstrated reliability and validity as a screening tool for psychiatric disorders in general hospital outpatients. A cut-off point of five showed adequate sensitivity (77.8%) and specificity (80.9%) for the depression subscale, and a cut-off point of eight showed adequate values of sensitivity (88.9%) and specificity (77.2%) for the anxiety scale (51).

**Generalized Anxiety Disorder-7 (GAD-7):** A simple seven-item tool to detect cases of generalized anxiety disorders. The adapted version for the Spanish population has a one-dimensional structure that matches the original structure based on the DSM-IV diagnostic criteria. A cut-off value of 10 showed adequate values of sensitivity (86.8%) and specificity (93.4%) (52).

**Center of Epidemiologic Studies-Depression (CES-D):** A self-rating scale composed of 20 items, designed to detect depressive symptomatology. It has been extensively used in ESRD (53). A cut-off value of 16 has shown adequate sensitivity (0.95) and specificity (0.91) in the Spanish validation study (54).

**Short Form 36 health questionnaire:** The SF-36 consists of eight domains yielding two summary measures: physical and mental health. The physical component includes four dimensions (physical functioning, role-physical, bodily pain, and general health); the mental health score is composed of vitality, social functioning, role-emotional, and mental health (55); the SF-36 has been validated for use in the general Spanish population (56).

**GLIM criteria:** The GLIM consensus is a three-step approach to assess malnutrition where patients are first identified by any validated screening tool (e.g., MUST) and then diagnosed if they meet at least one phenotypical characteristic (non-volitional weight loss, low body mass index, or reduced muscle mass) and one etiological criterion (reduced food intake or assimilation, disease burden, or inflammation); finally, severity is determined, based on threshold levels of the phenotypic criteria (57).

**SARC-F:** The SARC-F is a questionnaire to detect individuals who may have sarcopenia based on the assessment of five domains: strength, walking across a room, rising from a chair, climbing stairs, and number of falls in the last year. Each item is scored at one of three subjective levels of difficulty. The questionnaire has been validated for the Spanish population (58).

**European Working Group on Older People 2020 updated criteria (EWGSOP2):** The updated EWGSOP definition of sarcopenia is based on the presence of low muscle strength and low muscle mass (59).

**Temperament and Character Inventory-140 (TCI-140):** The TCI-140 consists of 140 items, of which 136 relate to the seven temperament and character domains (novelty seeking, harm avoidance, reward dependence, persistence, self-directiveness, cooperativeness, and self-transcendence), and the remaining four items measure response accuracy/carelessness. The TCI-140 represents a short form of the original Temperament and Character Inventory-Revised (TCI-R; 240 items) and has shown adequate reliability (alpha from 0.72 to 0.82) except for novelty seeking (alpha = 0.63) (60).

**Five Facets Mindfulness Questionnaire (FFMQ):** This 39-item self-administered questionnaire measures five facets of mindfulness (Observing, Describing, Acting with awareness, Non-judgmental, and Non-reactive); the Spanish version has shown adequate internal consistency (alpha ranging from 0.75 to 0.91) (61).

**Charlson Comorbidity Index:** This score was originally developed to evaluate prognosis based on weightings for specific comorbidities; each of these conditions is given a weighting of 1 to 6 and weighted scores are summed (62–64).

